Visit 1 (V1): is carried out on all subjects, in the nurses’ offices of the educational centres. V1 includes: anamnesis, physical examination, VCTE to assess LSM and CAP, and collection of the completed socio-demographic and medical history questionnaire. After V1, all subjects are scheduled for Visit 2 and Visit 3. In addition, subjects with altered results (CAP ≥225 dB/m and/or LSM ≥ 6.5kPa) and 10% of subjects with normal results are referred to Visit 4. Lastly, subjects with suspected significant fibrosis (LSM ≥6.5 kPa) are referred to the Digestive Service of the Hospital Universitari Germans Trias i Pujol (HUGTP) for further evaluation (Visit 5).Visit 2 (V2): is conducted at the educational centres and consists on lifestyle assessment (Diet Quality estimation with the KIDMED index [31]), physical activity (PA) assessment with the Physical Activity Unified-7 item Screener (PAU-7S) [32], and sedentary behaviour [33], sleep duration [34], and sugar consumption assessment) through online self-reported questionnaires with the assistance of trained personnel.Visit 3 (V3): is performed in the Primary Care Centres corresponding to each subject. In V3, all subjects undergo blood sampling. The samples are analysed in the HUGTP laboratory.Visit 4 (V4): is performed in the Diagnostic Imaging Centres located within the area of the educational centres. MRIs are performed on all subjects with CAP ≥225 dB/m and/or LSM ≥6.5 kPa and 10% of participants with CAP <225 dB and/or LSM <6.5 kPa.Visit 5 (V5): is performed in the Digestive Service of the HUGTP. Subjects with suspected significant fibrosis (LSM ≥6.5 kPa) undergo the corresponding diagnostic tests and follow-up according the Clinical Practice Guideline for the Diagnosis and Treatment of NAFLD in Children [25].

Finally, all subjects (whether they obtain CAP ≥225 dB/m and/or LSM ≥6.5 kPa or CAP <225 dB/m and/or LSM <6.5 kPa), and especially those with NAFLD risk factors such as obesity, DM, MetS or risky alcohol consumption are counselled on lifestyle modifications by the health care professionals involved in the study [35]. They are also referred to their corresponding healthcare providers for management of these risk factors according to each centre’s own protocol (Fig 1).

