LSM is performed in all patients using VCTE with the Fibroscan® (FS) system (Echosens, France). LSM is performed with S, M or XL probe following the Automatic Probe Selection tool available on the FS. The FS used is the 430 MINI. FS measures the hepatic elasticity of a cylinder approximately 1 cm in diameter by 4 cm in length [41]. FS transmits, via a probe, a vibration that propagates through the liver. The speed of propagation of the vibration correlates with the stiffness (in kPa) of the liver tissue and allows estimation of the fibrosis degree. In order for VCTE to be valid, 10 correct determinations with an interquartile range (IQR) <30 and a success rate >60% must be obtained. Significant liver fibrosis by VCTE is being defined by a LSM ≥6.5 kPa [13–16].Fibrosis scores/serum biomarkers: Pediatric NAFLD Fibrosis Index (PNFI) and Pediatric NAFLD Fibrosis Score (PNFS) are being used to estimate fibrosis degree. Significant liver fibrosis is being defined when the values of the different scores are above the following cut-offs, according to literature: PNFI ≥9, PNFS ≥13 [22, 23, 42, 43].

**Liver steatosis** is estimated using three methods: CAP, liver steatosis score and MRI.

CAP using VCTE is used to measure liver steatosis with the FS using either S, M or XL probe at the time of LSM. Liver steatosis is diagnosed when the value of CAP ≥225 dB/m [13–16].Liver steatosis is measured by the steatosis score Fatty Liver Index (FLI) which is based on: WC, BMI, TG and GGT [19]. Significant liver steatosis is defined when FLI ≥60 according to literature [44].Liver steatosis measured by MRI. It is performed using the Magneton Essenza 1.5 Tesla Aera system (SIEMENS), with the integration of Tim technology and Dot Engines (Day Optimizing through put Engines) application packages. The result obtained is the steatosis score or steatosis degree corresponding to the percentage of hepatocytes containing fatty vacuoles with respect to the hepatic fat fraction. Thus, a differentiation is made among mild steatosis (5–29% of hepatocytes affected), moderate steatosis (30–59% affected) and severe steatosis (more than 60% of hepatocytes affected). MRI is performed on all participants with altered VCTE results (≥6.5 kPa and/or ≥225 CAP) and 10% of participants with normal VCTE results (<6.5 kPa or <225 CAP).

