### Sample size calculation

The school population aged between 9 and 16 in Mataró stands at 11,503 individuals [45]. These are approximately equally distributed between the 4 groups: male/female between 9 to 12 and 13 to 16 years old.

We expect that 8% of this population will have NAFLD and 2% will have liver fibrosis. A sample size of 2,866 students will allow us to estimate a prevalence of NAFLD stratified by age (9–12, 13–16 years) and sex of 8%, with a precision of 2% in each stratum, and a prevalence of fibrosis of 2%, with a precision of 1% in each stratum. We anticipate that blood samples will be available in 50% of the sample and MRI in 70%. MRI will be offered to all LSM/CAP positive subjects (LSM ≥6.5 kPa / CAP ≥225 dB/m) and, randomly, to 10% of those with negative LSM/CAP (LSM <6.5 kPa / CAP <225 dB/m). This will add up to 1,433 blood tests and 424 MRIs.

With the proposed sample we can find a concordance of 80% with a precision of 4% using kappa indices, or an intraclass correlation coefficient of 0,8 with a precision of 2,5% (8% and 4% precision for kappa and ICC, respectively, using only 424 MRIs). This sample size has been calculated assuming a design effect of 20%, an alpha error of 5%, a power of 80% and bilateral contrasts.

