### Statistical analyses

Prevalences of NAFLD and fibrosis will be calculated using CAP ≥225dB/m and LSM ≥6.5kPa, respectively. They will be calculated by sex and age (9–12 and 13–16 years) and 95% confidence intervals will be provided.To determine the optimal CAP cut-off point that best fits the 4 MRI categories, the relationship between CAP and MRI will be explored graphically, CAP means for each MRI category will be compared by ANOVA, 2-to-2 ROC curves will be used, and a multi-class ROC curve will be used to obtain the overall area under the curve for the finally chosen points. In addition, dichotomous CAP classifications (normal/altered) will be compared with MRI levels using contingency tables and chi-square tests.To identify the variables related to NAFLD, multivariate models will be used using NAFLD as the dependent variable and possible risk and confounding factors as independent variables.Concordance between the diagnosis of NAFLD or fibrosis obtained by different methods (CAP vs FLI, LSM vs PNFI, LSM vs PNFS) will be assessed by kappa indices (when using the dichotomised version of these variables) and by the intraclass correlation coefficient (when using the continuous version of the variables). The best cut-off point in PNFI and PNFS will be chosen to detect fibrosis using LSM ≥6.5 kPa as the standard test in the diagnosis of fibrosis using ROC curves.The construction of the biomarker to detect the presence of steatosis in children and adolescents will be carried out using the coefficients of multivariate logistic regression models, where steatosis (CAP >225 dB/m) will be the dependent variable and the rest of the variables will be potential explanatory variables that may form part of the marker.

To take into account that participants come from selected schools, hierarchical models will be used when necessary. All tests will be bilateral, with a significance of 5%. We do not plan to use missing data imputation methods as we expect very few missings beyond those already considered. Stata17 statistical package will be used.

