### Risks and disadvantages for patients

There are minimal disadvantages for the subjects arising from their participation in this study. In fact, the only ones expected are the following: 1) Blood collection may be accompanied by discomfort or temporary swelling or bruising at the puncture site. All possible measures will be taken to minimise this effect. 2) MRI is not painful, non-invasive and does not use radiation, but the patient must remain in an enclosed machine, which may be a problem for claustrophobic patients. However we will explain that it is a completely harmless and safe procedure, that in no case will any type of medication, contrast or sedation be used, and that it is an opportunity to obtain health related relevant information. In the event that MRI is still not well tolerated by the patient, we will disregard it and offer it to another eligible subject. Meanwhile, VCTE is well tolerated and the procedure does not represent any potential risk for the patient or adverse effects. Thus, overall, the benefits of participating in this study outweigh the risks.

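### Selection for MRI depends on CAP and LSM, and the CAP-versus-MRI analysis states no correction for it, so sensitivity, specificity and the lowest cut-off will be biased if analysed as written

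*Protocol article*

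**What the plan says.** All of this comes from the protocol article.

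- **Who is scanned.** Study design (Visit 4), Data collection and measuring tools, and Sample size calculation all send every child with CAP ≥225 dB/m and/or LSM ≥6.5 kPa to MRI. They add one tenth of those with normal results, and the sample size section says that tenth is random.
- **How the 10% group is worded.** Study design has "10% of participants with CAP <225 dB and/or LSM <6.5 kPa". Data collection and measuring tools has "10% of participants with normal VCTE results (<6.5 kPa or <225 CAP". Sample size calculation simply contrasts positive with negative subjects.
- **How the scans are analysed.** Statistical analyses plans graphs, a comparison of CAP means across MRI categories by ANOVA, and "2-to-2 ROC curves will be used, and a multi-class ROC curve will be used to obtain the overall area under the curve". It then plans contingency tables with chi-square tests for CAP as normal or altered against MRI level. Hierarchical models for schools, when necessary, are the only allowance for how children were sampled. Imputation is not planned.
- **What is claimed.** Under Main outcome measures, the accuracy comparison of CAP with MRI is for the general population aged 9 to 16. The cut-off outcome refers to children and adolescents.
- **Intolerance of MRI.** Under Risks and disadvantages for patients, if the scan is not tolerated, "we will disregard it and offer it to another eligible subject".

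**The concern.** CAP is the test being evaluated and MRI is the reference. When CAP largely decides who gets the reference test, the scanned children are not a fair picture of the school population: those above 225 dB/m are heavily over-represented. This is partial verification bias. Sensitivity and specificity condition on the MRI result, so they change when the mix of CAP-positive and CAP-negative children is altered. A cut-off read from a ROC curve changes with them. Hierarchical models for schools do not address selection by CAP.

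The consequence is practical. The study proposes VCTE for screening in children. An analysis that under-counts missed steatosis would make the test look far more sensitive than it is, and would set the lowest CAP threshold too high.

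**Working it through.** **1. Reproducing the 424 MRIs.** Inputs from Sample size calculation: 2,866 students; "We expect that 8% of this population will have NAFLD and 2% will have liver fibrosis"; MRI availability of 70%; 10% of negatives scanned.

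- Positives: 0.70 × 0.08 × 2,866 = 160.5
- Negatives: 0.10 × 0.92 × 2,866 = 263.7
- Total: 424.2, which matches 424.

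Applying 70% to both groups gives 345, and applying it to neither gives 493. The stated figure therefore implies MRI fractions of 0.7 in positives and 0.1 in negatives, a 7:1 ratio. Positives are 8% of the children but 160.5/424.2 = 38% of the scans. This treats the 8% as the whole screen-positive group. Selection also uses LSM, but with only 2% expected above 6.5 kPa, CAP dominates.

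**2. Bias at 225 dB/m.** With MRI fractions a in positives and b in negatives, the unweighted results are

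- sensitivity = a·Se / [a·Se + b·(1 − Se)]
- specificity = b·Sp / [b·Sp + a·(1 − Sp)]

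Whenever a > b, the first exceeds the true Se and the second falls below the true Sp. The direction needs no further assumption; the size does.

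The documents give no true accuracy, so assume Se/Sp = 70%/95%:

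- Sensitivity: 0.7×0.70 / (0.7×0.70 + 0.1×0.30) = 0.49/0.52 = 94.2%
- Specificity: 0.1×0.95 / (0.1×0.95 + 0.7×0.05) = 0.095/0.130 = 73.1%

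This case fits the plan's 8% CAP-positive if MRI steatosis is 4.6%: 0.70p + 0.05(1 − p) = 0.08 gives p = 0.03/0.65. The 424 scans then hold about 65 true positives, 96 false positives, 4 false negatives and 260 true negatives. Missed steatosis appears as 6% when it is 30%.

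Over a range of assumptions (8% positive, PPV 40–80%, 1–4% of negatives with steatosis, 7:1):

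| | True | Unweighted |
|---|---|---|
| Sensitivity | 47–87% | 86–98% |
| Specificity | 95–98% | 72–89% |

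**3. Predictive values.** In the same example, PPV among the scanned is 64.8/160.5 = 40.4%. In the population it is 92.6/229.3 = 40.4%. Conditioning on the CAP result removes the selection, so PPV and NPV at 225 dB/m are not biased if attendance within each group is random.

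**4. Cut-offs.** The plan names no optimality criterion, so Youden is assumed, with normal CAP distributions and fractions of 0.7 above and 0.1 below 225 dB/m.

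None versus steatosis, mean (SD) in dB/m:

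| None | Steatosis | Full population | Unweighted | Shift |
|---|---|---|---|---|
| 175 (30) | 235 (40) | 206 | 228 | 22 |
| 170 (35) | 230 (45) | 203 | 229 | 26 |
| 165 (35) | 215 (40) | 192 | 218 | 26 |

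In simulations of these cases the area under the curve rose by about 0.03–0.04. Weighting by 1/0.7 and 1/0.1 brought the first case back to a cut-off of about 206 and Se/Sp at 225 dB/m of 60%/95%. Unweighted, that case read 91%/74%.

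For pairwise curves across the four MRI categories, with means 185/235/275/305 and SDs of 32–38, the shifts are about 22–23 (none/mild), 9–12 (mild/moderate) and 2–4 (moderate/severe). That scenario implies about 15% CAP-positive. Lower means of 170/230/270/300 with SDs 30/40/40/40, and category shares of 92/5.5/1.8/0.7%, give 8.3% positive and shifts of about 22, 15 and 5. The ordering is the same.

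**The case against.** The strongest defence is that the article is silent rather than wrong. It names families of methods, a fuller analysis plan may exist, and drawing the normals at random with a known fraction keeps valid weighting open. That stands to this extent: the article does not say the analysis will be unweighted, and a reader who infers a decision against weighting goes beyond the text. But the section sets out the CAP–MRI methods step by step, names the one sampling feature it will handle, and rules out imputation. Followed as written, it gives the biased result.

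Several stronger readings are tempting and are not supported:

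- **A 10:1 ratio and a collapse of specificity.** All positives are *offered* MRI, but 424 reproduces only with 70% uptake among them. At 10:1, an assumed 80%/90% would read as 97.6%/47.4%. With 8% steatosis, that case implies 0.08×0.80 + 0.92×0.10 = 15.6% CAP-positive, about twice the planned 8%.
- **All cut-offs moving by about 20 dB/m.** Comparing each severity level with everyone else suggests this, but the plan uses pairwise curves, where the main bias is at none/mild.
- **A general-population claim for the cut-offs.** That phrase is attached to the accuracy outcome, not to Aim 2 or the cut-off outcome.
- **Real doubt about who is scanned.** Read literally, the *or* and *and/or* wording puts a child with CAP ≥225 and LSM <6.5 in both groups. The contrast of positive with negative under Sample size calculation makes the intent clear, so this is a drafting fault.
- **Replacement across groups.** The replacement rule does not say which group a substitute comes from. Every positive is already offered MRI, so a lost positive has no unapproached positive to take its place. The article gives no figure from which to size the effect.

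**Conclusion.** The point holds. Selection for the reference test depends on the index test at about 7:1 by the plan's own figures, and the stated analysis does not correct for it, while accuracy is claimed for the general population. The direction at 225 dB/m is algebraic: sensitivity too high, specificity too low. The size rests on assumed accuracy: 70%/95% reading as about 94%/73% is a case consistent with 8% CAP-positive.

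The none/mild cut-off is pulled up by about 22–26 dB/m, given the assumed CAP distributions and a Youden criterion. The mild/moderate shift is smaller and the moderate/severe shift is small. PPV and NPV at 225 dB/m are not affected if attendance within each group is random.

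**What to change.** 1. In Statistical analyses, state that the CAP-versus-MRI ROC, cut-off and contingency analyses will be weighted by the inverse of the realised MRI fraction in two strata: CAP ≥225 and/or LSM ≥6.5; and CAP <225 and LSM <6.5. Intervals should respect both the weights and school clustering. Two strata are enough for the stated design.
2. In Study design and in Data collection and measuring tools, word the 10% stratum as CAP <225 **and** LSM <6.5.
3. Count MRI non-completers and replacements within their own stratum when computing the realised fractions.

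**Cost.** No new data are needed, only wording and a weighted analysis. The price is precision. With weights of 1/0.7 and 10, the Kish effective sample is (Σw)²/Σw² = 2,866² / (160.5×2.041 + 263.7×100) ≈ 308 of 424, a variance factor of about 1.38 before clustering. Sensitivity may suffer more than that average suggests: in the 70%/95% example it rests on about 4 scanned false negatives, each with weight 10. Weighting corrects the designed selection only. It does not correct attendance that depends on steatosis within a stratum, so that assumption should be stated.

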### Specific outcome measures

Comparison of liver steatosis diagnosis accuracy between CAP by VCTE and Fatty Liver Index (FLI) in the general population aged ≥9 to ≤16 years.Comparison of liver fibrosis diagnosis accuracy between LSM by VCTE and two fibrosis scores (Pediatric NAFLD Fibrosis Index and Pediatric NAFLD Fibrosis Score) in the general population aged ≥9 to ≤16 years.Detection and structuring of the variables that constitute a specific biomarker for the paediatric-juvenile population that is capable of accurately determining the presence of hepatic steatosis.Correlation of liver steatosis diagnosis using CAP by VCTE, FLI and MRI, with the presence of lifestyles and socio-economic factors associated with NAFLD in the general population aged ≥9 to ≤16 years.Percentage of subjects with BMI ≥30 in the general population aged ≥9 to ≤16 years.Percentage of subjects with MetS according to the International Diabetes Federation (IDF) consensus criteria for children and adolescents [36] in the general population aged ≥9 to ≤16 years.

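### CAP cut-offs are chosen and scored on the same MRI sample, which is slightly optimistic for the overall AUC and materially so at a sparse grade; the PNFI/PNFS cut-off to be used is left open

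*Protocol article*

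**What the plan says.** **CAP against MRI.** The second main aim is to find CAP cut-offs for mild, moderate and severe steatosis. Both the cut-offs and the accuracy of CAP against MRI are listed under Main outcome measures. The Statistical analyses section sets the task as "To determine the optimal CAP cut-off point that best fits the 4 MRI categories". It explores the relationship graphically, compares means by ANOVA, draws pairwise ROC curves, and closes with: "a multi-class ROC curve will be used to obtain the overall area under the curve for the finally chosen points". The sequence contains no second sample and no resampling step.

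**PNFI and PNFS against LSM.** This is one of the Specific outcome measures: "Comparison of liver fibrosis diagnosis accuracy between LSM by VCTE and two fibrosis scores". Two cut-off rules appear. Data collection and measuring tools defines significant fibrosis "according to literature: PNFI ≥9, PNFS ≥13". The Statistical analyses section says: "The best cut-off point in PNFI and PNFS will be chosen to detect fibrosis using LSM ≥6.5 kPa as the standard test". The same section says that agreement between methods "will be assessed by kappa indices (when using the dichotomised version of these variables", without saying which of the two cut-offs produces that dichotomy.

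**The concern.** A threshold picked because it performs best in a sample also exploits that sample's chance pattern. Sensitivity and specificity read off at that threshold in the same children are therefore too high on average, and the excess grows as the rarer group shrinks. An AUC computed after CAP has been collapsed at the chosen points inherits some of this. A ROC area on the continuous score does not.

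The study intends its CAP cut-offs to support screening in children. Overstated sensitivity would fall mainly on the rarest categories. For PNFI and PNFS, the two rules leave it open whether the reported agreement with LSM is a test of a published threshold or the result of a search.

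**Working it through.** **1. Counts from the plan's own figures (Sample size calculation).**

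Total: for fibrosis p = 0.02 and d = 0.01, n0 = 1.96² × 0.02 × 0.98 / 0.01² = 753. The finite-population correction with 11,503/4 children per stratum gives 597. Then 4 × 597 × 1.2 = 2,865.6, so 2,866 reproduces.

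Blood tests: 0.5 × 2,866 = 1,433, as stated.

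MRIs: 0.7 × 0.08 × 2,866 + 0.10 × 0.92 × 2,866 = 160.5 + 263.7 = 424, as stated.

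Two counts follow:
- About 160 VCTE-positive and 264 VCTE-negative children have MRI, to be spread over four MRI categories. The article does not say how many fall in each.
- LSM-positive children with blood: 0.02 × 1,433 = 28.7, about 29, against 1,404 negatives.

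**2. Method.** Scores are drawn from unit-variance normal distributions. The cut-off maximising the Youden index (sensitivity + specificity − 1) is chosen in the sample. Its apparent accuracy there is compared with its true accuracy under the generating distributions, averaged over 1,500 to 3,000 runs per setting.

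**3. Overall multi-class AUC for CAP (the statistic the plan names).** CAP is coded into four classes at three chosen cut-offs, and the pairwise areas are averaged. Grade counts and spacing between adjacent grades (0.7 or 1.0 SD) are assumptions.

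| Children per grade (none/mild/moderate/severe) | Spacing | AUC apparent / true | Excess | Severe sensitivity apparent / true |
|---|---|---|---|---|
| 264/80/50/30 | 0.7 | 0.742 / 0.727 | 0.015 | 85% / 80% |
| 264/110/40/10 | 0.7 | 0.755 / 0.734 | 0.022 | 87% / 76% |
| 264/120/35/5 | 0.7 | 0.767 / 0.735 | 0.032 | 90% / 72% |
| 264/80/50/30 | 1.0 | 0.807 / 0.793 | 0.014 | 93% / 88% |
| 264/110/40/10 | 1.0 | 0.819 / 0.800 | 0.019 | 95% / 84% |
| 264/120/35/5 | 1.0 | 0.828 / 0.801 | 0.028 | 97% / 79% |

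The overall AUC is overstated by 0.014 to 0.032. Sensitivity at the severe cut-off is overstated by about 5 to 6 points with 30 severe cases, 11 to 12 with 10, and 17 to 18 with 5.

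**4. A single CAP cut-off, assumed AUC 0.85, 424 scans.**

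| Positives | Youden apparent / true | Sensitivity apparent / true |
|---|---|---|
| 40 | 0.58 / 0.52 | 80% / 75% |
| 20 | 0.60 / 0.51 | 83% / 74% |
| 10 | 0.64 / 0.50 | 85% / 72% |

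Unrounded, the excess in sensitivity is 5.7, 8.9 and 13.8 points.

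**5. PNFI and PNFS, 29 against 1,404.** The inputs are the AUROCs given in the Introduction (PNFI 0.85, PNFS 0.74).

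| Score | Youden apparent / true | Excess | Sensitivity apparent / true |
|---|---|---|---|
| PNFS | 0.42 / 0.33 | 0.09 | 73% / 65% |
| PNFI | 0.59 / 0.52 | 0.07 | 81% / 74% |

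Nearly all the excess lies in sensitivity, because positives are scarce. As a control, the mean AUC of the continuous score was 0.741 and 0.848 against true values of 0.74 and 0.85, so it is not inflated. The chosen cut-off is also unstable: at AUC 0.74, 95% of simulated cut-offs span about 1.4 SD of the score.

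**The case against.** **The article is condensed.** Internal validation may be described in a full protocol or SAP that is not shown. This stands as a limit: a reader might infer that no correction is planned anywhere, and the article cannot support that. It does, however, print the sequence from exploration to final performance, and its last step is a figure for the selected points. The point concerns that sequence.

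**The named statistic is barely affected.** This stands. A reader might take the larger sensitivity figures as the bias in the overall AUC. They are not; that bias is about 0.01 to 0.03. The larger figures apply to sensitivity or the Youden index at a sparse grade, which the article does not expressly promise to report, although CAP accuracy against MRI is a main outcome.

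**For PNFI and PNFS only selection is stated.** This also stands. A reader might infer that the plan reports accuracy at the derived cut-offs, but the text says only that they will be chosen. Kappa may well use the published values. What remains is that two rules exist and the analysis text does not say which applies.

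**Sampling error is larger than the bias.** With 29 positives and sensitivity 0.73, the simple 95% half-width is 1.96 × √(0.73 × 0.27 / 29) = 0.16, above the 0.07 to 0.09 excess. This is true, but an uncorrected interval would be centred too high and would still ignore the search.

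**Conclusion.** The point holds in limited form. For CAP, the described sequence selects and scores cut-offs in the same children, so the reported performance is optimistic. The excess is about 0.01 to 0.03 for the overall multi-class AUC, and about 6 to 14 points of sensitivity at a grade with 40 down to 10 positives. For PNFI and PNFS the finding is conditional: a Youden index overstated by about 0.07 to 0.09 if results are reported at the derived cut-off.

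The count of 29 and the total of 424 follow from the article. The CAP figures rest on assumed grade counts, an assumed AUC or grade spacing, normal scores and a Youden criterion. The PNFI and PNFS figures carry published AUROCs over to an LSM reference in schoolchildren. School clustering and selection into MRI by VCTE result are ignored. The calculations do not show that the cut-offs themselves are biased in one direction; they show inflated apparent accuracy and, with few positives, an unstable cut-off.

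**What to change.** - **CAP.** Report performance at the chosen cut-offs (overall AUC, and sensitivity and specificity per grade) with bootstrap optimism correction. Resample schools and repeat the whole cut-off search in each resample. Give a bootstrap 95% confidence interval for each cut-off, and state the number of children per MRI grade beside it.
- **PNFI and PNFS.** State that the published cut-offs, "PNFI ≥9, PNFS ≥13", are used for the main kappa and accuracy comparison with LSM. Label the re-derived cut-offs exploratory, with the same correction and intervals.

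No new data are needed. The cost is a bootstrap loop, a few sentences of text, and slightly less favourable accuracy figures.

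### The intraclass correlation planned for CAP vs FLI, LSM vs PNFI and LSM vs PNFS depends on the measurement scales and on the ICC form, so it cannot be read as agreement

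*Protocol article*

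**What the plan says.** Statistical analyses in the protocol article names three pairs and two statistics. The diagnoses from "CAP vs FLI, LSM vs PNFI, LSM vs PNFS) will be assessed by kappa indices" in their dichotomised form, and "by the intraclass correlation coefficient (when using the continuous version of the variables") in the other case. It gives no ICC form (one-way, absolute agreement or consistency) and no rescaling of either variable.

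Data collection and measuring tools shows what is being paired:

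- CAP is in dB/m: "Liver steatosis is diagnosed when the value of CAP ≥225 dB/m".
- FLI is a composite score, the "Fatty Liver Index (FLI) which is based on: WC, BMI, TG and GGT", with its own threshold: "Significant liver steatosis is defined when FLI ≥60 according to literature".
- LSM is in kPa: "Significant liver fibrosis by VCTE is being defined by a LSM ≥6.5 kPa".
- The two fibrosis scores have cut-offs "PNFI ≥9, PNFS ≥13".

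Sample size calculation says the study can estimate "an intraclass correlation coefficient of 0,8 with a precision of 2,5" per cent, or 4% if only the 424 MRIs are used. It does not say which comparison the ICC belongs to.

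**The concern.** An ICC treats two numbers from one child as repeat readings of the same quantity on the same scale. That does not hold for any of the three pairs. A child exactly at both steatosis cut-offs has readings of 225 and 60. An absolute-agreement ICC counts the difference of 165 as disagreement, although it has no unit. At the fibrosis cut-offs the differences are 2.5 (6.5 vs 9) and 6.5 (6.5 vs 13).

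The value then reflects the units, the spread of each measure and the form selected in the software, as well as how well one measure tracks the other. A score that follows CAP or LSM closely could be reported as agreeing poorly. Choosing the form, or adding a standardisation, after seeing the data could largely determine the answer. These comparisons serve listed outcomes under Specific outcome measures.

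**Working it through.** **1. The plan's own figures.** Sample size, using 2% fibrosis, ±1% per stratum, four strata of 11,503/4 = 2,875.75 and a design effect of 1.2:

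- n0 = 1.96² × 0.02 × 0.98 / 0.01² = 752.9
- with finite population correction: 752.9 / (1 + 751.9/2,875.75) = 596.9
- 596.9 × 1.2 × 4 = 2,865, against the stated 2,866.

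The total therefore reproduces from the fibrosis precision and does not rest on the ICC.

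Precision of an ICC of 0.8 for two readings, half-width = 1.96 × (1 − 0.8²) / √(n/1.2 − 1):

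- n = 424: 0.7056/18.77 = 0.038 (stated 4%; agrees after rounding)
- n = 1,433: 0.7056/34.54 = 0.020
- n = 2,866: 0.7056/48.86 = 0.014

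The stated 2.5% is not reproduced exactly but is on the conservative side. That arithmetic is not the problem.

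**2. ICC when the two measures correspond perfectly (r = 1).** With means m1, m2 and SDs s1, s2, in a large sample:

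- absolute agreement = 2·s1·s2 / [s1² + s2² + (m1 − m2)²]
- consistency = 2·s1·s2 / (s1² + s2²)

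The documents give no means or SDs, so every mean (SD) below is an assumption. Rows marked * set the means at the protocol's cut-offs.

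| Pair | Assumed mean (SD) | Absolute agreement | Consistency |
|---|---|---|---|
| CAP, FLI | 200 (40), 15 (15) | 1,200/36,050 = 0.03 | 1,200/1,825 = 0.66 |
| CAP, FLI | 190 (45), 20 (20) | 1,800/31,325 = 0.06 | 1,800/2,425 = 0.74 |
| CAP, FLI* | 225 (40), 60 (25) | 2,000/29,450 = 0.07 | 2,000/2,225 = 0.90 |
| CAP, FLI | 200 (40), 15 (40) | 3,200/37,425 = 0.09 | 3,200/3,200 = 1.00 |
| LSM, PNFI | 4.8 (1), 4 (3) | 6/10.64 = 0.56 | 6/10 = 0.60 |
| LSM, PNFI* | 6.5 (1), 9 (3) | 6/16.25 = 0.37 | 6/10 = 0.60 |
| LSM, PNFS | 4.8 (1), 10 (8) | 16/92.04 = 0.17 | 16/65 = 0.25 |
| LSM, PNFS* | 6.5 (1), 13 (8) | 16/107.25 = 0.15 | 16/65 = 0.25 |
| LSM, PNFS | 4.5 (1), 15 (10) | 20/211.25 = 0.09 | 20/101 = 0.20 |
| LSM, PNFS | 4.8 (1), 13 (1) | 2/69.24 = 0.03 | 2/2 = 1.00 |

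Every row describes a perfect correspondence, yet the ICC runs from 0.03 to 1.00.

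A one-way ICC at r = 1 is (4·s1·s2 − d²) / (2·s1² + 2·s2² + d²), with d = m1 − m2. For CAP and FLI the first row gives (2,400 − 34,225)/(3,650 + 34,225) = −0.84. The equal-SD row gives (6,400 − 34,225)/(6,400 + 34,225) = −0.68.

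**3. Effect of units.** One simulated LSM–PNFI sample (n = 1,433; LSM 4.8 (1), PNFI about 4 (3)) had a Pearson correlation of 0.63:

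| LSM expressed as | Absolute agreement | Consistency |
|---|---|---|
| kPa | 0.36 | 0.38 |
| kPa × 10 | 0.02 | 0.35 |
| kPa × 1,000 (that is, Pa) | 0.00 | 0.00 |
| both variables z-scored | 0.63 | 0.63 |

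The correlation is 0.63 in every row. After standardisation the ICC is simply Pearson's r.

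**The case against.** There are four fair objections.

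- **The form is open.** If a consistency ICC is meant, the difference in means drops out, and CAP vs FLI can give 0.66 to 1.00 at r = 1. This stands against a stronger reading that a reader might infer: that the planned statistic is bound to be near zero or negative, or that 0.8 is out of reach. The article fixes no form. LSM vs PNFI gives 0.37 to 0.56 even under absolute agreement, and standardised variables could reach 0.8. The consistency form still varies with the SD ratio alone, so it does not rescue the interpretation.
- **The details may be in a full analysis plan that is not shown.** The ICC form and a standardisation step could be there. However, the article itself commits to an ICC for these pairs with no such step. If the variables were standardised, a correlation should be named.
- **Little hangs on it.** The comparisons are specific outcomes and not main ones. They also have kappa, and PNFI and PNFS have ROC curves against LSM ≥6.5 kPa. This stands and limits the severity.
- **The precision statement is not tied to these pairs.** Its parenthesis refers to the MRIs. This also stands, so it needs restating only so far as it is meant for these comparisons.

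**Conclusion.** The point holds in a limited form. For these three pairs the ICC as planned is scale-dependent and form-dependent, and cannot be interpreted as agreement. That rests on the units and cut-offs in the article. The sizes rest on assumed means and SDs. At r = 1, absolute agreement is about 0.03 to 0.09 for CAP vs FLI and 0.37 to 0.56 for LSM vs PNFI. For LSM vs PNFS it is 0.09 to 0.17 with a PNFS SD of 8 or 10, and 0.03 if both SDs are 1. Consistency runs from about 0.2 to 1.00 with the SD ratio.

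It would be wrong to infer that the study's planning fails. The total of 2,866 does not depend on the ICC, and the prevalence estimates, kappa and ROC analyses are untouched. This is a should-fix point on secondary outcomes.

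**What to change.** - In Statistical analyses, replace the ICC for CAP vs FLI, LSM vs PNFI and LSM vs PNFS by a Spearman (or Pearson) correlation with 95% CI. Describe it as association, since a correlation does not measure agreement.
- Keep kappa for the dichotomised versions and the ROC analyses of PNFI and PNFS as planned.
- In Sample size calculation, so far as the ICC of 0.8 is meant for these pairs, restate it as the precision of a correlation of 0.8. For Pearson's r, with the 1,433 expected blood tests and the design effect of 1.2, the Fisher interval is about 0.78 to 0.82 (±2.0%).

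The cost is a sentence or two in each section, with no new data and no burden on participants. The change should be made before these comparisons are analysed, so that the statistic is not chosen with the results in view.
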